Similarly, little is known about the changes in the target tissue (myocardium) that are brought about by RIPC *before* ischemia and reperfusion. Most studies that have investigated changes in the myocardium have done so *after* reperfusion. It has been suggested that a signalling factor triggers intracellular signal transduction mechanisms in the heart, which are similar to those involved in cardiac ischaemic pre- and post-conditioning [1]. These could include activation of pro-survival kinases of the reperfusion injury salvage kinase (RISK) pathway, which could protect the heart by inhibition of the mitochondrial permeability transition pore (MPTP) [1]. It is possible that a variety of other signalling pathways involved in MPTP regulation [31] could also be involved in RIPC-induced protection. A recent experimental study [32] investigated the differential role of mitogen-activated protein kinase pathways, which suggested that the phosphorylation of p38MAPK, Erk1/2 and JNK could be involved in RIPC. Experimental evidence supports involvement of the mitochondrial Ca^2+^-activated K^+^ channel [33]. A very recent observational clinical study reported that RIPC was associated with changes in the phosphorylation of the signal transducer and activator of transcription 5 (STAT5) [11]. Most of these studies point to the mitochondria as a potential target for inducing protection by RIPC. We hypothesise that kinases involved in regulating the permeability of the MPTP are the mediators of RIPC-induced cardioprotection. Therefore, these enzymes and related signalling pathways will be monitored to identify the main pathway(s) responsible.

A key difference that is likely to exist between RIPC and cardiac pre- and post-conditioning stimuli (where the heart is made ischaemic for short periods) is related to changes in energy rich phosphates. Thus, RIPC is not expected to trigger cardiac changes associated with anaerobic metabolism (for example, drop in ATP, and build-up of ATP catabolites and lactate). However, a recent experimental study in mice has demonstrated that RIPC is associated with cardiac ischaemic stress and accumulation of cardiac adenosine prior to index ischaemia [34]. This highlights the need to measure ischaemic-stress related metabolites in the hearts of patients undergoing surgery using RIPC.

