#### Markers in myocardial biopsies

The degree of ischaemic stress (anaerobic metabolism) associated with RIPC and cardioplegic arrest will be determined in ventricular biopsies. The metabolites that will be investigated in the ventricular biopsies are creatine phosphate, ATP, ADP, AMP, IMP, inosine, xanthine, hypoxanthine, adenosine, NAD^+^, lactate, alanine and glutamate. In addition, markers of potential signalling pathways that could be involved in RIPC will be monitored [23]. These secondary outcomes will be analysed in biopsies from the majority of participants, with a subgroup (about ten per group) being used for analyses of protein expression.

Expression of proteins implicated in RIPC protection in experimental studies will be determined by characterising the activation of intracellular kinases [35-37], the activation of the reperfusion injury salvage kinase (RISK) pathway, and the survivor activating factor enhancement (SAFE) pathway [38]. Gene expression for proteins that are activated will also be determined. Recent technological advances have provided new tools for screening and characterisation of activated proteins including mass spectrometry [39]. This is particularly important at the level of post-translational modifications of proteins (for example, phosphorylation), which are largely responsible for regulation of protein activity and function [40,41]. Therefore, the cardiac phosphoproteome will be measured in order to draw firm conclusions about the functional relevance of changes in proteins (proteome). A recent study has shown that RIPC cardioprotection in mice is linked with significant changes in several phosphoproteins associated with the z-disk area of the sarcomere [39]. Several of the phosphoproteins identified do not have antibodies available, thus making it difficult to measure using conventional methods. Therefore, we shall use these methods to screen for protein activation.

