### Sample size

Cardiac Troponin I is measured at the start of the operation (before RIPC or sham RIPC), after applying RIPC or sham RIPC, and five times after the end of ischaemic cardioplegic arrest and CPB. Determining an appropriate sample size requires several parameters to be specified. We have estimated some parameters from our previous research: average pre-post correlation = 0.3 and average post-post correlation = 0.5. We propose to recruit 30 patients/group in each surgical stratum, giving a sample size of 60 per surgical stratum and a total of 120. This sample size for each stratum is similar to that used in a previous trial in which RIPC was observed to have induced significant cardio-protection during CABG surgery [8]. Assuming an analysis of variance and covariance, this sample size will have 90% power to detect a standardised difference in serum markers of 0.43 between groups providing that there is no interaction between intervention/control and pathology. If there is an interaction, the sample size of 60 for each pathology will have 80% power to detect a standardised difference in serum markers of 0.55 between groups within each pathology stratum.

Assuming again an analysis of variance and covariance but without repeated measures, the sample size of 60 per group (assuming no interaction between intervention/control and pathology) will have 90% power to detect a standardised difference in cellular markers of 0.6 between groups. If there is an interaction, the sample size of 60 will have 80% power to detect a standardised difference in cellular markers of 0.72 between groups within each pathology stratum. Based on our previous research analysing myocardial biopsies, differences of this magnitude are plausible [46-49].

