### Changes to the protocol since first approved

Substantial and minor amendments have been made. Inclusion and exclusion criteria have been amended to include a wider age range of patients and to facilitate recruitment. The primary outcome was changed from Troponin T to Troponin I because the coordinating centre measures Troponin I routinely. The type of blood sample collection was clarified in terms of distinguishing between serum and plasma concentrations. Anaesthetic details were removed to allow the operating team to follow their local practice. A more complete list of expected adverse events was added. Novel proteomic analyses on biopsies collected in a subgroup of participants have been added to characterise potential mechanistic pathways for RIPC. The sample size was increased by 25% to allow the proteomic analyses to be carried out in a subset of participants and to allow the trial to detect a smaller target difference between groups within each surgery stratum separately. The current version of the protocol is version 3 dated 17 July 2014.

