In order to monitor the changes in biomarker outcomes, blood samples are collected at various time points during a participant’s hospital stay. Some of these blood sample collections are scheduled outside office working hours. Even though reminders about the need to collect these samples are ‘handed over’ to the clinical team in charge of the patient when shifts change, on some occasions sample collection may be missed due to lack of time and other priorities. Similarly, there may be instances in which the biopsies are not collected; we aim to minimise this risk by having a member of the research team present in the theatre to prompt the operator to take the biopsies.

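### The single power statement for cellular markers assumes all 60 participants per group and does not hold for the protein-expression subset of about ten per group

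*Protocol article*

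**What the plan says.** The Sample size section plans "30 patients/group in each surgical stratum, giving a sample size of 60 per surgical stratum and a total of 120". For tissue outcomes it drops the repeated-measures gain used for serum markers and makes two claims. Overall, "the sample size of 60 per group (assuming no interaction between intervention/control and pathology) will have 90% power", for a standardised difference of 0.6. Within a stratum, "the sample size of 60 will have 80% power to detect a standardised difference in cellular markers of 0.72 between groups". Both are made for cellular markers as a class, with no exception. The paragraph closes by calling differences of that size plausible on the strength of earlier biopsy work.

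Markers in myocardial biopsies describes a different number of assays. After listing the metabolites and mentioning signalling-pathway markers, it says these outcomes will be "analysed in biopsies from the majority of participants, with a subgroup (about ten per group) being used for analyses of protein expression". Challenges in study procedures adds that "there may be instances in which the biopsies are not collected".

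Changes to the protocol since first approved says "The sample size was increased by 25% to allow the proteomic analyses to be carried out in a subset of participants". The same sentence then gives a second purpose: detecting a smaller target difference within each surgical stratum.

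**The concern.** A power statement should refer to the participants who will supply the outcome. Here one statement covers every cellular marker and credits each with the full randomised sample, while another section of the article gives one family of those markers roughly a sixth of that number per arm (10/60), or a third (20/60) on the more generous reading of group.

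The protein work bears on the mechanistic aim. The Background states: "We hypothesise that kinases involved in regulating the permeability of the MPTP are the mediators of RIPC-induced cardioprotection". A reader who meets an inconclusive protein-expression result, and looks up what the trial could have detected, will find 90% power at 0.6 SD and may take the result as evidence against an effect of that size. With about ten per group it would be no such evidence.

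**Working it through.** **Inputs**
- 60 per arm overall and 30 per arm per stratum; 0.6 SD at 90% and 0.72 SD at 80% (Sample size).
- About ten per group for protein expression, and most participants for the other biopsy markers (Markers in myocardial biopsies).
- Two-sided alpha of 0.05. This is an assumption, in line with the 95% confidence intervals in Plan of analysis.
- SD = 1 and no covariate gain, because this reproduces the plan's own figures.

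**Formulas** (normal approximation, n per arm)
- Power = Φ(d/√(2/n) − 1.96)
- Detectable difference = (1.96 + z)·√(2/n), with z = 1.2816 for 90% and 0.8416 for 80%

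**Step 1: the plan's figures**
- n = 60, d = 0.6: 0.6/√(2/60) = 3.286; Φ(3.286 − 1.96) = 90.8%. Stated: 90%.
- n = 30, d = 0.72: 0.72/√(2/30) = 2.789; Φ(2.789 − 1.96) = 79.6%. Stated: 80%.

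Both agree. Sixty per arm is 2 × 60 = 120, and 30 per arm in two strata is 4 × 30 = 120. Nothing is held back for unassayed or missing tissue.

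**Step 2: the protein-expression subset**

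| Reading of group | n per arm | Power at 0.6 SD | Detectable at 80% | Detectable at 90% |
|---|---|---|---|---|
| Arm | 10 | Φ(1.342 − 1.96) = 26.8% | 2.8016 × √(2/10) = 1.25 SD | 3.2416 × √(2/10) = 1.45 SD |
| Arm within stratum | 20 | Φ(1.897 − 1.96) = 47.5% | 2.8016 × √(2/20) = 0.89 SD | 3.2416 × √(2/20) = 1.03 SD |

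The noncentral t gives slightly lower power: 24.5% at 10 per arm and 45.6% at 20.

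Within a stratum at 0.72 SD, power is 36.3% with 10 per arm, and 20.6% with 5 per arm (ten per arm split evenly over two strata). The stated figure is 80%.

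**Step 3: the other biopsy markers**

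Most participants is fewer than 60 per arm, but no number is given. If, and only if, the subset's tissue is not also used for metabolites:
- 50 per arm left: power at 0.6 SD is Φ(3.000 − 1.96) = 85.1%; detectable at 90% is 3.2416 × √(2/50) = 0.65 SD.
- 40 per arm left: power is Φ(2.683 − 1.96) = 76.5%; detectable at 90% is 3.2416 × √(2/40) = 0.72 SD.

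These two lines illustrate a possible assay plan. They do not measure a known shortfall.

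**The case against.** **The arithmetic in the plan is right.** That stands. The fault lies in the scope of the term cellular markers, not in the calculation.

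**A covariance adjustment would recover power.** The Sample size section does name analysis of covariance. With its pre-post correlation of 0.3, 50 per arm would have 88.2% power at 0.6 SD. But that correlation is given in the troponin calculation; applied at 60 per arm it yields 93.1% rather than the stated 90%; and the first biopsy is taken after RIPC or sham, so tissue has no pre-intervention baseline. Even if the gain is granted, the subset reaches only 29.0% at 10 per arm and 51.2% at 20.

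**The small subset is disclosed and looks exploratory.** In part. The number is printed, the proteomic methods are described as a screen, and confidence intervals would show the imprecision. Yet the power paragraph exempts nothing.

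Three stronger readings are tempting, and the article does not support them:
- *That the ten are taken out of the metabolite assays.* The wording also fits a nested subset. Four biopsies are collected per participant, and nothing reserves tissue for one assay.
- *That the 25% increase is counted twice.* The stated second purpose, a smaller within-stratum difference, means the added participants were intended to count there. The increase implies 120/1.25 = 96 before it, or 24 per arm per stratum, where the 80% detectable difference is 2.8016 × √(2/24) = 0.81 SD, against 0.72 SD at 30.
- *That all kinase outcomes rest on ten per group.* The sentence assigning outcomes to most participants follows the mention of signalling markers. Ventricular biopsies describes Western blotting of ERK1/2, GSK3β and Akt with no restriction to a subset, and Plan of analysis puts kinase activity through the general mixed model. Against this, the biopsy section treats kinase activation as the means of determining protein expression. The question is open.

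**Conclusion.** The point holds for the protein-expression and proteome subset. The article's 90% at 0.6 SD becomes about 27% with 10 per arm, or about 48% with 20 per arm, and neither reading of group comes near the stated power. For the remaining biopsy markers the stated power is somewhat too high, because fewer than 60 per arm will be assayed and some biopsies may be missed; the size of that gap cannot be fixed from the article. Whether the kinase markers share the severe shortfall depends on an assay plan that the sections describe inconsistently.

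The figures rest on a two-sided 5% level, equal arms and no covariate gain. These are secondary outcomes and the troponin calculation is separate, so this should be corrected but does not threaten the primary analysis.

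**What to change.** - Limit the cellular-marker power statement, and the sentence calling such differences plausible, to markers assayed in all or nearly all participants, and recompute it with the n actually planned. For example, if the subset's tissue is not also used for metabolites, quote 0.65 SD (50 per arm) or 0.72 SD (40 per arm) at 90% power.
- Give the protein-expression and proteome subset its own n and detectable difference (about 1.25 SD at 80% power for 10 per arm, or 0.89 SD for 20), and label it exploratory.
- Reconcile Markers in myocardial biopsies, Ventricular biopsies, Sample size and Plan of analysis on two matters: whether group means arm or arm within stratum, and which kinase and signalling markers are measured in the subset and which in most participants.

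The cost is a few sentences and less favourable figures. No extra participants or assays are needed.

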### Statistical analyses

#### Plan of analysis

Continuous outcomes will be summarised and presented graphically as geometric means and standard errors, assuming that a natural logarithmic transformation will be applied to the data to normalise their distributions [50]. The primary outcome, Troponin-I, and the secondary outcomes such as markers of kinase activity, oxidative stress and inflammation, are all measured multiple times in each patient (see Table 1). Therefore, Troponin-I and the other markers will be analysed by fitting multilevel mixed effect linear regression models, which consider the repeated measures in an appropriate and efficient manner. These models will fit both fixed effects (intervention, surgical stratum, centre, time and the interactions of intervention x time and intervention x centre) and a random effect. The fixed effects are analogous to standard regression coefficients and are estimated directly. The random effect is not directly estimated but is summarized according to its estimated variances and covariance. Baseline (pre-intervention) measures, where available, will be analysed jointly with the post-intervention measure(s). The interaction of group and surgical stratum will be tested and, if statistically significant at the 10% level, the treatment effect will be reported for each stratum separately; otherwise, an overall treatment effect will be given. Similarly, interactions of group and time and group and centre, will be explored (overall or within stratum depending on the significance of the group by stratum interaction) and, if statistically significant at the 10% level, the treatment effect will be reported for each time point separately.

Analyses will be adjusted for stratification factors, namely surgical procedure and centre. Findings will be reported as effect sizes with 95% confidence intervals. Analyses will be based on the intention-to-treat; cross-overs are expected to be rare. The frequencies of complications and conversions will be tabulated descriptively, by pathology. However, the trial is not powered to detect differences in adverse events and no statistical comparisons will be carried out.

It is important to emphasise that analyses of all outcomes will adjust for baseline levels of outcomes. Therefore, although there will be heterogeneity between patients within groups, the analyses will take this heterogeneity into account by quantifying the effects of the design factors after removing variation attributable to individual participants. This approach extends to the analyses of the proteome/phosphoproteome since data will be available for biopsies from the same ventricle of the same participant before and after cardioplegic ischaemic arrest. In effect, this allows us to focus on detecting changes in the same tissue (left or right ventricle) in two different pathologies.

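### Taken literally, the listed mixed model lets the arms differ at the pre-RIPC sample, so it does not give the baseline-adjusted precision behind the 90% power for troponin I

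*Protocol article*

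**What the plan says.** Three statements in the protocol article bear on baseline.

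- **Sample size.** The calculation uses "average pre-post correlation = 0.3 and average post-post correlation = 0.5". It then says: "Assuming an analysis of variance and covariance, this sample size will have 90% power to detect a standardised difference in serum markers of 0.43". That claim is made only for the case where intervention and pathology do not interact. The numbers are: "We propose to recruit 30 patients/group in each surgical stratum, giving a sample size of 60 per surgical stratum and a total of 120".
- **Plan of analysis, model.** The model has "fixed effects (intervention, surgical stratum, centre, time and the interactions of intervention x time and intervention x centre"), plus one random effect. On baseline: "Baseline (pre-intervention) measures, where available, will be analysed jointly with the post-intervention measure(s"). An overall treatment effect is reported unless an interaction reaches the 10% level. The contrast that makes up this overall effect is not defined.
- **Plan of analysis, closing paragraph.** It stresses that "analyses of all outcomes will adjust for baseline levels of outcomes".

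Troponin I is measured once before RIPC or sham, then "after applying RIPC or sham RIPC, and five times after the end of ischaemic cardioplegic arrest and CPB".

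**The concern.** Once the pre-RIPC value is one of the outcome records, an intervention main effect plus intervention by time allows a separate arm difference at every time, including baseline. With complete data, the intervention effect after arrest is then the plain difference in post-arrest means, and the baseline record adds nothing to it. If the effect is instead read from the interaction terms with baseline as the reference time, it is a full change from baseline. Neither is the covariance-adjusted effect that the 0.43 SD figure rests on.

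There is a further risk. If intervention by time is not significant and is dropped while baseline stays in the outcome, the single remaining intervention term averages over a time at which treatment cannot have acted. That pulls the primary estimate towards zero.

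At stake are the precision, and in the last case the size, of the primary troponin estimate.

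**Working it through.** **Inputs.** From Sample size: 60 per arm overall, pre-post correlation 0.3, post-post correlation 0.5, one baseline and five post-arrest samples, effect 0.43 SD. Assumed: two-sided 5% (the sample size text gives no alpha), complete data, equal variances, and an effect that is the same at all five post-arrest times.

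**Variance factors** (arm-difference variance = 2 × factor / n, in SD² units):

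- Mean of five post-arrest values: (1 + 4 × 0.5)/5 = 0.60
- Baseline as covariate: 0.60 − 0.3² = 0.51
- Change from baseline: 0.60 + 1 − 2 × 0.3 = 1.00

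Generalised least squares on the six-record outcome vector gives the same values. A joint model with equal baseline means has factor 0.51, identical to analysis of covariance. A joint model with free baseline means has 0.60 for the post-arrest difference and 1.00 for the change.

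**The plan's own figure.** With factor 0.51, SE = √(2 × 0.51/60) = 0.130 and 0.43/0.130 = 3.30. Power is Φ(3.30 − 1.96) = 91.0% (90.5% by noncentral t). The stated 90% reproduces, and it needs the baseline-adjusted factor.

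**Free baseline.**

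- Post-arrest difference: SE = √(2 × 0.60/60) = 0.141, ratio 3.04, power 86.0% (85.4% by t). About 69 per arm would be needed for 90%.
- Change from baseline: SE = √(2 × 1.00/60) = 0.183, ratio 2.36, power 65.4% (64.7% by t). About 114 per arm would be needed.

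**One intervention term over all six records.** Put weight w on baseline and 1 − w on the post-arrest mean. The variance factor is w² + 0.60(1 − w)² + 2 × 0.3 × w(1 − w), and the expected estimate is (1 − w) × 0.43.

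- Equal weights, w = 1/6: factor 0.528, expected estimate 0.358 (83% of the true effect), SE 0.133, power 77.1% (76.4% by t).
- Least-squares weights, w = 0.3: factor 0.09 + 0.294 + 0.126 = 0.51, expected estimate 0.301 (70%), SE 0.130, power 63.6% (62.9% by t).

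| Analysis at 0.43 SD, 60 per arm | Factor | Share of effect estimated | Power (normal) |
|---|---|---|---|
| Equal baseline means, or baseline covariate | 0.51 | 100% | 91.0% |
| Free baseline, post-arrest difference | 0.60 | 100% | 86.0% |
| Free baseline, change | 1.00 | 100% | 65.4% |
| Single term, equal weights | 0.528 | 83% | 77.1% |
| Single term, least-squares weights | 0.51 | 70% | 63.6% |

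Counting the sample taken straight after RIPC as a sixth post value moves the first three powers only to 91.8%, 86.9% and 66.1%, and only if the effect is already present at that time.

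**The case against.** The strongest reply is that the document never says the arms may differ at baseline. Joint modelling with equal baseline means is a standard form of baseline adjustment, and here it equals analysis of covariance. On that reading, Sample size and both parts of Plan of analysis agree. The fixed-effects list is plainly not exhaustive: it omits intervention by surgical stratum, which the same paragraph says will be tested. It also serves every marker, including biopsy markers with no pre-RIPC sample, for which an intervention main effect is needed. The separate analysis plan could settle the coding.

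Much of this stands. A reader might infer that the document contradicts itself, that troponin is not baseline-adjusted at all, or that the 90% power is missed outright. The text supports none of these. The free baseline difference follows from the listed terms and is not stated. The change contrast does adjust, by subtraction, though inefficiently. The power loss depends on which contrast is used.

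The within-stratum claim of "80% power to detect a standardised difference in serum markers of 0.55 between groups within each pathology stratum" does not help the argument either. It lies closer to the unadjusted factor (77-79%) than to the adjusted one (83-85%). Nor does the article's remark on urgent admissions say anything about troponin imbalance between randomised arms. With free baseline means, both contrasts are unbiased on average under randomisation.

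What does not stand is that this is only missing detail. The protocol names its terms, and a statistician who fits those terms gets a less precise or diluted estimate.

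**Conclusion.** The point holds as a conditional one. Fitted literally, the listed terms with baseline in the outcome do not deliver the promised baseline adjustment or the precision behind 90% power at 0.43 SD. The loss is about 5 points for the post-arrest difference and about 26 points for the change contrast. It is about 14 to 27 points, with the effect diluted, if one term spans the baseline record. Dropping the interaction is itself a reading of the 10% rule, which does not say whether the term is removed.

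The figures assume the plan's correlations, complete data, two-sided 5% and a constant post-arrest effect. The 91% for the constrained model also assumes that the fitted covariance can carry both correlations. The wording should be corrected, but the sample size need not change.

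**What to change.** In Plan of analysis, for outcomes with a pre-RIPC sample (troponin I and the blood markers), state one of the following:

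- the joint model is kept, with arm means constrained equal at the pre-RIPC time, so that intervention terms enter only at later times; or
- log baseline is a covariate and is removed from the outcome vector.

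Biopsy markers should be exempted, because the first biopsies are taken after RIPC and are not a pre-intervention baseline.

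Define the overall treatment effect as an average over post-intervention times only. Say whether the sample taken straight after RIPC, before arrest, is part of that average.

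This costs two or three sentences and needs no further patients or data. Power at 0.43 SD stays at about 91%, and both parts of Plan of analysis then agree with the 90% figure under Sample size.

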## Methods/Design

### Aims and objectives

The overall aim of the trial is to investigate the cardioprotective effect of RIPC in patients having CABG or aortic valve replacement surgery. Specific objectives are:To estimate the difference in myocardial injury following CPB and cardioplegic arrest in groups of participants exposed to RIPC or sham RIPC.To test whether the effect of RIPC versus sham RIPC differs in participants having CABG compared to participants having aortic valve replacement.To investigate a range of possible signalling mechanisms that may underpin a cardioprotective effect.

No RIPC represents standard clinical practice in the two centres.

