### Measurement of outcomes

#### Blood samples

Seven blood samples will be collected from each participant: two samples will be collected before the sternonotomy is performed and before CPB (one before RIPC and one after RIPC) is started, and five post-operative samples will be collected at 6, 12, 24, 48 and 72 hours after the end of ischaemic cardioplegic arrest. Each sample will amount to approximately 10 ml of blood stored in separate vials for plasma and serum analysis.

Serum concentration of Troponin I will be measured using automated assays. Plasma concentrations of IL-6, IL-8, IL-10 and TNFα will be measured using enzyme-linked immunosorbent assays (ELISA) or enzyme immunoassay (EIA) as described previously [42]. ATP catabolites, MDA, lactate and other relevant metabolites in plasma will be measured using HPLC and enzymatic kits as described above. In addition, plasma lactate and blood pH will be monitored at the same time points to determine the extent of systemic metabolic stress.

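### The test of whether RIPC works differently in AVR and CABG uses a time-constant interaction that includes troponin samples taken before cardiac arrest, which shrinks the estimated difference (by 2/7 on the literal reading, 1/6 if baseline only adjusts)

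*Protocol article*

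**What the plan says.** The second objective (Aims and objectives) is: "To test whether the effect of RIPC versus sham RIPC differs in participants having CABG compared to participants having aortic valve replacement". The first objective places the injury of interest after bypass and cardioplegic arrest, and the Discussion expects a larger effect in AVR.

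The Plan of analysis fits a mixed model to the repeated log troponin values. Its fixed effects are "intervention, surgical stratum, centre, time and the interactions of intervention x time and intervention x centre", plus one random effect that is not specified further. On baseline and on objective 2 it says: "Baseline (pre-intervention) measures, where available, will be analysed jointly with the post-intervention measure(s). The interaction of group and surgical stratum will be tested". The level of that test is 10%. If it is significant, effects are reported by stratum; otherwise one overall effect is given. Group x time is explored afterwards, overall or within stratum according to that result. Neither stratum x time nor group x stratum x time is named. A later paragraph of the same section adds that the analyses of all outcomes adjust for baseline.

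The Blood samples section sets the schedule. On the early draws it says: "two samples will be collected before the sternonotomy is performed and before CPB (one before RIPC and one after RIPC) is started". The remaining five draws all come after arrest, the first at 6 h and the last at 72 h.

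**The concern.** A two-way group x stratum term in a repeated-measures model is one shift applied to every sample among the outcomes. The overall RIPC effect may vary with time, because intervention x time is in the model. The AVR-CABG difference in that effect may not.

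Two of the seven samples cannot carry the difference that objective 2 asks about. Before RIPC, any arm-by-stratum difference is chance. Immediately after RIPC the heart has not yet been arrested, so there is no arrest injury to be protected from. Averaging these samples into the contrast pulls it towards zero, against the trial's own hypothesis. The result of this test also decides whether stratum-specific effects are reported at all.

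**Working it through.** **Inputs from the article.** Sample size: "We propose to recruit 30 patients/group in each surgical stratum, giving a sample size of 60 per surgical stratum and a total of 120". Correlations: "average pre-post correlation = 0.3 and average post-post correlation = 0.5". Two pre-arrest and five post-arrest samples. Interaction tested at 10%.

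**Assumptions, not in the article.** The 10% test is two-sided. The correlation between the two pre-arrest samples is *r* = 0.5 to 0.9. SDs are equal at all times and data are complete. The true difference is zero in the first two samples and constant over the last five. The intervention x centre term is left out.

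**1. The plan's own figure.** With five post samples and one baseline covariate, the variance factor is V = (1 + 4 x 0.5)/5 - 0.3² = 0.51. At 60 per group, SE = sqrt(2 x 0.51/60) = 0.130. For 0.43 SD, 0.43/0.130 - 1.96 gives 91.0% power at two-sided 5%, against the stated 90%, so it reproduces. The stated 80% at 0.55 SD concerns the effect within one stratum. The article gives no target and no power for the interaction.

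**2. Contrast on the five post-arrest samples, pre-RIPC value as covariate.** The interaction is a difference of differences over four cells of 30, so SE = sqrt(4V/30) = sqrt(4 x 0.51/30) = 0.261. All of the true difference is kept.

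**3. Literal reading: all seven samples as outcomes, random intercept (equal weights).** The share kept is 5/7 = 0.714. V = (7 + 2*r* + 20 x 0.3 + 20 x 0.5)/49, which is 0.490 at *r* = 0.5 and 0.506 at *r* = 0.9. SE = 0.256 to 0.260.

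**4. Baseline as covariate, post-RIPC sample still an outcome, equal weights over six.** The share kept is 5/6 = 0.833. V = (6 + 10 x 0.3 + 20 x 0.5)/36 - ((*r* + 5 x 0.3)/6)², which is 0.417 at *r* = 0.5 and 0.368 at *r* = 0.9. SE = 0.236 to 0.221.

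**5. Power for an assumed 0.65 SD.** Power = Phi(0.65 x kept/SE - 1.645). The difference detectable with 80% power is (1.645 + 0.842) x SE/kept.

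| Analysis | Kept | SE | Power at 0.65 SD | Detectable at 80% |
|---|---|---|---|---|
| Post-arrest contrast | 1 | 0.261 | 80% | 0.65 SD |
| Literal, seven samples | 0.714 | 0.256-0.260 | 56-57% | 0.89-0.90 SD |
| Baseline adjusted, six samples | 0.833 | 0.236-0.221 | 74-79% | 0.70-0.66 SD |

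At other true sizes, post-arrest versus literal (*r* = 0.5) power is 50% v 33% at 0.43 SD, 68% v 46% at 0.55 SD, 95% v 78% at 0.86 SD and 99.5% v 92% at 1.10 SD.

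**6. Unequal weights.** If the fitted covariance follows the article's correlations, the two pre-arrest samples take 40%, 35% and 32% of the weight at *r* = 0.5, 0.7 and 0.9, and shrinkage is the same percentage. With baseline as covariate and efficient weights, the share kept is 0.625, 0.50 and 0.25, a shrinkage of 38-75%.

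**7. Role of stratum x time.** In the literal model with complete data, the coefficient (0.714) and SE (0.256) are the same with or without it. If the group effects are constrained to zero at baseline, the result changes. When AVR and CABG differ by 1 SD in their post-operative rise and the term is omitted, the estimate moves from 0.833 to 1.391 of a true 1 SD. That is a leak of 1.391 - 0.833 = 0.558 SD. With the term in the model the estimate returns to 0.833.

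**The case against.** The strongest reply is that the literal reading may not be what is meant. The article stresses adjustment for baseline, and modelling baseline jointly with later values is compatible with no group effect at baseline. Only the post-RIPC sample then dilutes the contrast. With equal weights the smaller SE recovers most of the loss, and power is 1 to 6 points below the post-arrest contrast. This stands, and it means that 29% is not a floor. The article does not say which reading applies, and the estimate is still shrunk by 1/6.

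A constrained baseline without stratum x time can even look more powerful (86% at an assumed 0.64 SD, against 73% with the term). That precision is borrowed from assuming parallel CABG and AVR curves. Step 7 shows the bias when they are not parallel.

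A second reply is that covariance structure, baseline coding and higher-order terms belong in an analysis plan that is not shown. That is fair for such detail. Here, however, the article itself lists the fixed effects, places baseline with the outcomes and names the two-way test.

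Three stronger inferences are tempting, and the article does not support them:

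- **A fall in power from 80% to about 56% as a fact.** It needs an interaction size and a pre-pre correlation that are nowhere given.
- **The missing stratum x time term as the cause of the shrinkage.** Step 7 shows that it is not.
- **A non-significant test being presented as equal effects in both operations.** The plan says only that an overall effect will then be reported.

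**Conclusion.** The point holds. As written, objective 2 is tested with a time-constant contrast that spans samples in which the difference sought cannot yet exist. With an effect confined to, and constant over, the five post-arrest samples, the estimate is shrunk by 2/7 (29%) on the literal reading with a random intercept. If baseline is a covariate or constrained, the shrinkage is 1/6 (17%) with equal weights. Efficient weighting makes it larger in both cases.

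The shrinkage under equal weights rests on the sampling schedule and that effect pattern. The power figures rest on more: the assumed 0.65 SD, *r* between 0.5 and 0.9, equal SDs, complete data and no intervention x centre term. They are illustrations of a loss that may be large or slight depending on how baseline is coded. The missing stratum x time term is a separate weakness, which matters if baseline is constrained.

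**What to change.** In the Plan of analysis, define the objective 2 contrast as the AVR-minus-CABG difference in the RIPC-versus-sham effect on log troponin I, averaged over the 6, 12, 24, 48 and 72 h samples and adjusted for the pre-RIPC value. Report the immediately post-RIPC sample separately. Add stratum x time to the fixed effects, so that a different post-operative rise in the two strata cannot leak into the interaction estimate if baseline stays in the outcome vector.

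The cost is wording and a few degrees of freedom: stratum x time takes four with five sample times in the model, or six with seven (7 x 120 = 840 planned values). No new patients or samples are needed. The downside is that the post-RIPC sample no longer contributes to this test. The article reports recruitment as ongoing and plans no formal interim analysis, so the change can be made before the primary analysis.
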